### Informed consent

2.6

The informed consent procedure will be conducted in an open, transparent manner and will strictly adhere to ethical standards. Parents or guardians of children meeting the inclusion and exclusion criteria will receive a comprehensive written explanation describing the research objectives, procedures, potential risks and benefits, as well as data privacy protection measures. This includes detailed information on how their data will be collected, stored, and protected. We will ensure that all data is securely stored in encrypted form on protected servers, accessible only to authorized research team members during the study period, and properly destroyed after the study concludes. Participants will be given sufficient time to carefully read the consent form, ask any questions, and provide consent voluntarily. They will be explicitly informed that they have the right to withdraw from the study at any time without any negative consequences. The research team will provide ongoing contact information for consultation, allowing participants to obtain further information or clarification when needed. Throughout the study, we will provide participants with any new information that might affect their decision to continue participation, ensuring continuous informed consent.

Additionally, participants will not face any penalties for deciding to withdraw from the intervention arm. If the intervention has already commenced, patients cannot switch to the control group after withdrawal and will be marked as an attrition case. Where feasible, semi-structured interviews will be conducted with attrited participants to explore reasons for discontinuation. During the informed consent process, participants will be explicitly informed of all available options following withdrawal, ensuring they remain fully aware of their rights and choices throughout the study period.

### Interventions

2.7

#### Control group: standard treatment group

2.7.1

Participants assigned to the control group will receive standard medical care delivered by a multidisciplinary clinical team. This care includes: 1) regular physician consultations for health assessment and treatment plan adjustments; 2) scheduled follow-up visits at predefined intervals to monitor disease progression; 3) comprehensive diagnostic evaluations to track health indicators; 4) structured health education sessions focusing on condition management, treatment adherence, and lifestyle modifications; and 5) evidence-based referrals to specialized care providers when clinically indicated. This integrated approach ensures alignment with clinical practice guidelines while maintaining ethical research standards and routine asthma management protocols.

#### Intervention group: standard treatment + AI-HEALS

2.7.2

Building on previous pediatric asthma RCTs (28, 29), this study adopted a 3-month intervention duration. During the three-month period, the AI-HEALS intervention will be delivered to the intervention group via the ‘Children’s Asthma Health Management Expert’ WeChat platform. The intervention team comprises public health experts, clinicians, clinical nurses, psychologists, and statistical analysts, each contributing their unique expertise to the intervention design. The intervention program comprises the following four core components:

Children’s Asthma Knowledge-Based Intelligent Question-Answering System (KBQA): This program aims to help parents of asthmatic children better understand asthma. It plays a role through the FAQ robot (FAQrobot), so that families can efficiently and accurately obtain the knowledge related to childhood asthma. In order to achieve this goal, we will develop a thorough and accurate knowledge base around childhood asthma. The knowledge base will cover a wide range of aspects, including the basic concepts of disease, etiology, symptoms, treatment methods, drug use, daily management, appropriate diet and appropriate sports activities. We will integrate this knowledge base into the large language model of Doubao (developed by ByteDance). In this way, the model can learn from the database and provide professional answers to patients’ questions directly on the WeChat platform. In addition, in order to enhance the interaction and user participation, the system will ask three related questions each time the user queries. This encourages users to explore further and interact more deeply with the system. In order to continuously optimize the knowledge base and better meet the needs of users, we will record the query and usage behavior of participants at the back end of the system, such as the time and frequency of accessing the system. By analyzing this data, we can identify the patterns of participants’ behavior. Based on these insights, we will be able to adjust and improve the knowledge base and question-and-answer system to ensure that the information is up-to-date and accurate. In the whole question-and-answer interaction process, the system supports text and voice input. This greatly reduces the threshold for users operating the system, so that more people can access the system.Recording and Monitoring of Physiological Indicators and Lifestyle Changes: In this study, the AI-HEALS will be used to encourage childhood asthma families to regularly record lifestyle factors, including weekly medication adherence, dietary habits, and physical exercise. Participants can directly input data into the system, allowing researchers to review recorded content in real-time through a backend interface, enabling long-term tracking and monitoring of self-management behaviors. To ensure data relevance and accuracy, the research team will jointly develop SMART (Specific, Measurable, Achievable, Relevant, Time-bound) plans with families during the initial phase of engagement. Data collection processes will be structured around these plans, with system-generated reminders sent every Saturday prompting detailed information uploads. This approach allows comprehensive assessment of intervention impacts on patients’ daily lives while ensuring data alignment with family-specific goals.Customized Reminder Services: In order to improve treatment compliance, the AI-HEALS system will provide a personalized reminder service. Participants can flexibly set reminders for various important tasks, such as medication and exercise. Once these reminders are set, the system will automatically send notifications at the specified time. This reminder service is designed to help patients strictly abide by medical advice, promote the long-term sustainability of healthy behaviors, and ultimately help to better control asthma.Automated and Personalized Asthma Science Articles for Family: The system will also run a mechanism to automatically distribute educational articles. Every week, families of children with asthma will automatically receive one to three articles on asthma management. These articles will cover a variety of topics. It includes dietary recommendations, such as which foods are good for asthmatic children and which foods should be avoided. Sports suggestions will also be provided to guide children to carry out sports activities of the appropriate type and intensity. It will also provide information on the correct medication, such as the correct method of medication and potential side effects that should be paid attention to. According to the interactions between the family and the system, such as the types of questions they raised, the frequency of visits, and the topics they are more interested in, targeted educational articles will be pushed accurately to meet the unique needs of each family. In order to maximize the effectiveness of information dissemination, the research team will regularly review the background data. This includes analyzing the number of articles that the participants visited, the different types of articles they liked, and the length of time they spent reading each article. According to this data, the article content and dissemination frequency will be adjusted.

The “Doubao-pro-32k” large language model (LLM) used in this study is a Chinese-trained Transformer-based architecture optimized for medical knowledge application. It was developed using a combination of biomedical literature and asthma-specific clinical guidelines, with fine-tuning conducted on a 32k context window to enable generation of long-form health education content. Prior to domain-specific fine-tuning, the model underwent extensive general language understanding pre-training to enhance its medical reasoning capabilities. Performance benchmarking was conducted using the third-party evaluation platform FlagEval (https://flageval.baai.ac.cn), where “Doubao-pro-32k” demonstrated competitive scores compared to GPT-4o. Specifically, Doubao-pro-32k attained an overall score of 77.75, surpassing GPT-4o’s 73.51. Its most distinguishing advantage lies in knowledge application (Doubao-pro-32k: 91.14 vs. GPT-4o: 86.71), a capability particularly crucial for generating evidence-based clinical information. Upon completion of development, an initial review of the model’s outputs was conducted by experts in the field to ensure that the information it generates matches well with existing medical knowledge and meets the high standards required for clinical research. In addition, at the end of the Pilot RCT, this study will set up a continuous validation process in which two experts will continuously review 10% of the outputs back to back on a monthly basis and calculate their correctness rate to maintain the accuracy of the system.

Finally, within the scope of this study, it is very important to protect the privacy of participants and ensure data security during their interaction with the AI-HEALS system. Any patient information obtained through the AI-HEALS platform will be treated with the strictest confidentiality and will only be used for research purposes. Each member of the research team is bound by the relevant privacy and confidentiality agreements. This means that they have a legal and moral obligation to protect the participants’ sensitive data. In addition, participants have the right to unconditionally withdraw from the study at any stage without providing any reason. This right respects the autonomy of participants and ensures that they will not be forced to continue participating in research. In addition, all adverse events related to the intervention will be recorded and reported in detail in strict accordance with local regulations and established procedures.

### Strategies to improve adherence to interventions

2.8

To encourage participant adherence, we will (1) provide a comprehensive explanation of participants’ responsibilities during the observation period, both in the recruitment program and when signing the informed consent form. Simultaneously, we will work to establish strong relationships with participants, aiming to foster mutual trust. (2) Throughout the research, researchers will offer all-round education and guidance regarding disease management and preventive measures. This involves elaborating on the characteristics of the disease, underscoring the significance of strictly following the treatment plan, and sharing strategies for preventing potential complications. (3) On a weekly basis, the research team will assess the interaction between the intervention group and the system. This is to make sure that participants are sufficiently engaged. Regular monitoring allows for timely identification of any issues or disengagement, enabling the team to take corrective actions and keep participants involved.

### Outcomes

2.9

#### Primary outcomes

2.9.1

The primary outcome was changes in asthma symptom control, measured using the Childhood Asthma Control Test (C-ACT) at baseline, discharge, and post-intervention. Given the nested longitudinal structure of repeated measurements within families, we employed multilevel negative binomial models to analyze asthma symptom frequency (count data), estimating incidence rate ratios (IRRs) and 95% confidence intervals (CIs).

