### Questionnaires

2.11

Childhood Asthma Control Test (C-ACT): The C-ACT is an important tool for measuring how well asthma symptoms are controlled in children. It has two parts with a total of seven questions in Chinese version. The first part has four questions for the child to answer. Each question is scored from 0 to 3, based on how the child feels about their asthma control. The second part has three questions for the parent to answer. Each question is scored from 0 to 5, based on how often the child has asthma symptoms in the last four weeks. The total score of the C-ACT goes from 0 to 27. A score of 23 or higher means asthma is fully controlled, with few symptoms affecting daily life. A score between 20 and 22 means partial control, where symptoms are somewhat managed, but some problems remain. A score of 19 or less means asthma is not controlled, and stronger treatments may be needed (31).Short-Form Egna Minnen av Barndoms Uppfostran for Chinese (s-EMBU-C): The s-EMBU-C is a questionnaire designed to evaluate how children see their parents’ parenting styles. The child fills out this questionnaire. There are separate versions for fathers and mothers. Each version has 21 questions, divided into three parts: rejection (6 items), emotional warmth (7 items), and overprotection (8 items). The questions are scored using a scale from 1 to 4. “Never” gets 1 point, “Occasionally” gets 2 points, “Frequently” gets 3 points, and “Always” gets 4 points. Item 15 is scored in reverse. The scores for each part are found by adding up the points for each question in that part. A higher score in a part means the parent shows that parenting style more often. The total score for both versions can range from 28 to 112 points (32).The assessment of depression and anxiety will use the Chinese version of the Patient Health Questionnaire-4 (PHQ-4). This is a short self-report tool to check depression and anxiety symptoms over the past two weeks. The PHQ-4 has four questions. The first two questions focus on depression symptoms, and the last two focus on anxiety symptoms. Each question is rated on a scale from 0 to 3: “Not at all” (0 points), “Several days” (1 point), “More than half the days” (2 points), and “Nearly every day” (3 points). The total score goes from 0 to 12. In studies in China, the PHQ-4 has shown high validity and reliability, with a Cronbach’s alpha of 0.833 (33).The Chinese version of the Perceived Social Support Scale-Short Form (PSSS-SF) is used to measure the level of social support a person feels they receive. The scale has three questions, each about a different type of support: family support (Item 1), friend support (Item 2), and other support (Item 3). Each question is scored on a 7-point scale from 1 (Strongly Disagree) to 7 (Strongly Agree). The total score can range from 3 to 21. Higher scores mean more social support, showing that the person’s social network provides more help, both emotionally and practically (34).The Chinese version of the New General Self-Efficacy Scale (NGSES-SF) is used to measure a person’s confidence in their ability to succeed in tasks or face challenges. It has three questions, each focusing on a different aspect of self-efficacy. Item 1 looks at how capable a person feels in handling a situation. Item 2 focuses on how confident a person is in their skills. Item 3 looks at how confidence in one area can apply to other areas. The NGSES-SF uses a 5-point Likert scale. Respondents can choose from 1 (Strongly Disagree), showing low confidence, to 5 (Strongly Agree), showing high confidence. The total score can range from 3 to 15 (35).The Chinese version of the EQ-5D-5L scale (EuroQol-5 Dimensions 5 Levels) will be used to measure quality of life. The scale looks at five important health areas: mobility, self-care, usual activities, pain/discomfort, and anxiety/depression. For each area, there are five levels, ranging from “no problems” to “extreme problems.” This lets respondents choose the level that best matches their condition. It gives a complete view of a person’s health in these five areas. The EQ-5D-5L also includes a Visual Analogue Scale (VAS). This part lets participants rate how they feel about their current health on a scale from 0 to 100. A score closer to 0 means worse health, while a score closer to 100 shows better health (36).Smoking behavior will be assessed using a self-designed questionnaire. The questionnaire has four multiple-choice questions to categorize smoking habits. These questions are meant to find out: whether the person smokes, how long it has been since they quit smoking (if they quit), how many cigarettes they smoke daily, and when they started smoking. The first question is “Do you have a smoking habit?” with these options: (1) Yes, I smoke regular cigarettes; (2) Yes, I smoke e-cigarettes; (3) I smoke both; (4) I used to smoke (now quit); (5) I have never smoked. Based on their answers, participants will be grouped into two categories: smokers, which include people who currently smoke regular cigarettes, e-cigarettes, or both; and non-smokers, which include those who have never smoked and those who have quit smoking (37).Alcohol consumption will be evaluated using a self-developed 7-item multiple-choice questionnaire designed to assess: 1) current/historical alcohol use status, 2) age of drinking initiation, 3) age of drinking cessation (if applicable), 4) preferred alcoholic beverage types, 5) average daily alcohol intake, 6) pre-quitting daily consumption volume, and 7) perceived anxiety related to alcohol cessation. The instrument begins with the core screening question: ‘Which best describes your alcohol consumption pattern?’ Respondents choose from four mutually exclusive categories: (1) Never consumed alcohol; (2) Current regular drinker; (3) Former drinker who has quit; (4) New-onset drinker in the past year (43, 44).The Chinese version of the Pittsburgh Sleep Quality Index Short Form (PSQI-SF) is a shorter version of the Pittsburgh Sleep Quality Index, made to measure sleep quality. The scale has six items, covering five key aspects of sleep. Items 1 and 2 measure sleep efficiency. Item 3 measures how long it takes to fall asleep. Item 4 looks at sleep duration. Item 5 checks for sleep disturbances. Item 6 looks at overall sleep quality. The total score on the PSQI-SF goes from 0 to 15. A higher score means worse sleep quality (38).The Chinese version of the Family Communication Scale Short Form (FCS-SF) is made to measure how well family members communicate. The scale has four items that assess family communication. It uses a 5-point Likert scale, where 1 means “strongly disagree” and 5 means “strongly agree.” The total score goes from 4 to 20. A higher score means better communication among family members (39).The Chinese version of the Electronic Health Literacy Scale (eHEALS) measures how well parents of children can search for, evaluate, and use electronic health information to solve health problems. The scale has five items in one dimension. It uses a 5-point Likert scale, where 1 means “strongly disagree” and 5 means “strongly agree.” The total score ranges from 5 to 25. A higher score means better electronic health literacy (40).

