
### Statistical analysis

2.12

This study will collect quantitative data through questionnaires and process the data using Microsoft Excel. Data analysis will follow the intention-to-treat principle. For continuous variables, descriptive statistics will show means ± standard deviations or medians and interquartile ranges (P25, P75), depending on the data. Normally distributed continuous variables will be compared using the Student’s t-test or one-way analysis of variance (ANOVA). Non-normally distributed data will be analyzed with non-parametric tests. The normality of the data will be checked using the Kolmogorov-Smirnov test. Categorical variables will be shown as sample percentages (n) and analyzed using the Chi-square test. For missing data, multiple imputation using chained equations (MICE) will be used, with 50 iterations to ensure convergence. The imputation method will be predictive mean matching (PMM), with 5 neighbors and 20 imputed datasets.

In the cross-sectional data analysis, this study will use linear regression, logistic regression, and structural equation modeling (SEM) to examine the relationships between behavioral patterns and mobile health applications. Given the nested structure of parent-child dyads within families, we employed multilevel models with family-level random intercepts to account for within-family correlations. For child health outcomes (asthma-related events and symptoms), a two-level negative binomial model was utilized to estimate IRRs and 95% CIs, adjusting for family-level variables (parents’ parenting styles, household income, marital status) and child-level variables (age, sex). For parental outcomes (continuous data), a two-level linear mixed model was applied to evaluate intervention effects, adjusting for family-level variables (marital status, household income) and parent-level variables (age, education, parents’ parenting styles). *Post hoc* comparisons of estimated marginal means were conducted using the emmeans package to test between-group differences. Model fit was validated through convergence checks, residual analysis, and overdispersion testing for count data. All analyses were performed in R (version 4.3.1; R Foundation for Statistical Computing, Vienna, Austria) using the lme4 package (version 1.1-33). An independent statistician with no conflicts of interest conducted the analysis. All statistical tests were two-tailed, with a significance level of 0.05.

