Based on this, the study will conduct a pilot randomized controlled trial to assess the effectiveness and acceptability of the AI-HEALS system in controlling asthma in children. The main purpose was to evaluate whether the intervention of C-ACT measurement after the intervention improved the control of asthma symptoms. Secondary outcomes include physical health indicators such as lung function, BMI, and hospitalization rates, as well as behavioral and psychological outcomes related to parental involvement, self-management strategies, and overall child quality of life. These outcomes will be measured using quantitative methods (e.g., standardized questionnaires and physiological assessments) and qualitative interviews. Given the medical and behavioral factors involved in childhood asthma, AI-HEALS has great potential to increase patient engagement and improve adherence to treatment regimens.

Although the interventions proposed in this study show considerable potential, some limitations must be recognized. First, the generalizability of the findings may be limited by inclusion criteria that focus on specific populations and clinical characteristics. For example, this study focused on children with asthma who were willing to use digital health interventions and may not have included those with lower health literacy or those less comfortable using technology. Second, while this study will provide valuable insights into the efficacy of the AI-HEALS system, there may be challenges in interpreting the numerous external factors that influence asthma control. Environmental triggers, socioeconomic status, and access to healthcare are all important variables that may influence outcomes, but it may be difficult to fully control for them in the real world. This study will include demographic and clinical covariates in its analysis in an attempt to account for some of these factors, although residual confounders may still affect outcomes. Finally, although the study aims to ensure data accuracy through rigorous monitoring procedures, issues such as participant dropout or missing data may still affect the validity of the findings. The research team plans to use multiple interpolation techniques to address these challenges, but the potential bias of missing data must still be considered.

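### The primary outcome spans three C-ACT visits with no named contrast, and the printed covariates omit baseline C-ACT but include parenting style, which is also measured after allocation

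*Protocol article*

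**What the plan says.** All references are to the protocol article.

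- **Section 2.9.1 (Primary outcomes).** Change in symptom control is "measured using the Childhood Asthma Control Test (C-ACT) at baseline, discharge, and post-intervention". The analysis is introduced with "Given the nested longitudinal structure of repeated measurements within families" and consists of "multilevel negative binomial models to analyze asthma symptom frequency (count data"). No primary visit, group-by-time term or contrast is named.
- **Section 2.11 (Questionnaires).** The three parent items of C-ACT are scored "based on how often the child has asthma symptoms in the last four weeks". No recall window is given for the four child items.
- **Section 2.12 (Statistical analysis).** The model for child outcomes is described as "adjusting for family-level variables (parents’ parenting styles, household income, marital status) and child-level variables (age, sex"). Baseline C-ACT is not in the list. Groups are then compared as follows: "comparisons of estimated marginal means were conducted using the emmeans package to test between-group differences". Again no visit is named.
- **Table 1 (section 2.10).** C-ACT and the parenting-style scale (s-EMBU-C) are both collected at time 0, discharge and 3 months.
- **Sections 2.2 and 2.5.** Families are invited when the child is admitted, so discharge falls one hospital stay after entry. Length of stay appears only as a secondary outcome (section 2.9.2), without a figure.
- **Section 5 (Discussion).** "The main purpose was to evaluate whether the intervention of C-ACT measurement after the intervention improved the control of asthma symptoms". This is the only place that singles out the post-intervention score.

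**The concern.** Three visits with no named contrast leave open what the primary estimate is. The three visits do not carry the same information about a three-month programme. At discharge a child has been exposed for at most one hospital stay, and much of what the parent items recall may lie before admission, in days that the baseline score already covers. An estimate that gives discharge the same weight as month 3 would understate the effect that the Discussion says is the target.

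Two further choices concern the covariates. Baseline C-ACT is collected but is not in the adjustment list, which matters for precision with about 25 children per arm. Parenting style is in the list without a visit attached. If values taken after allocation entered the model, and a family-directed intervention had changed them, adjustment could remove part of the effect being estimated.

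**Working it through.** **Inputs.** From the document: C-ACT at three visits (2.9.1, Table 1); four-week recall for the parent items (2.11); entry at admission (2.5); about 25 per group before allowance for attrition (2.4); two-sided 0.05 (2.12). Not in the document, and therefore assumed: length of stay L, the correlation r between baseline and month-3 C-ACT, the ratio f of the discharge effect to the month-3 effect, and any effect size or SD. The plan states no figure on this point that could be reproduced. The calculations treat C-ACT as a score on a linear scale with equal variance at each visit.

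**1. What discharge C-ACT looks back on.** The parent items make up 3 × 5 = 15 of the 27 points, and the child items 4 × 3 = 12. The share of a 28-day recall that precedes admission is 1 − L/28.

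| Assumed stay (days) | Share before admission |
|---|---|
| 5 | 82% |
| 7 | 75% |
| 10 | 64% |
| 14 | 50% |
| 21 | 25% |
| 28 | 0% |

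The share exceeds one half for any stay under 14 days. If the baseline score is taken at admission, those same days also lie in its recall window.

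**2. Size of the dilution, if visits are pooled.** With one group effect and equal weights, the estimate as a fraction of the month-3 effect is (1 + f)/2 over the two later visits and (1 + f)/3 over all three, baseline contributing zero.

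| f | Discharge and month 3 | All three visits |
|---|---|---|
| 0 | 0.50 | 0.33 |
| 0.25 | 0.63 | 0.42 |

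With a group-by-time term and a contrast at month 3, the fraction is 1 and nothing is lost.

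**3. Precision at month 3.** Adjusting for baseline multiplies the variance of the month-3 comparison by 1 − r², and so the standard error by √(1 − r²), ignoring the one degree of freedom used.

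| r | √(1 − r²) | Cut in standard error |
|---|---|---|
| 0.3 | √0.91 = 0.954 | 5% |
| 0.5 | √0.75 = 0.866 | 13% |
| 0.7 | √0.51 = 0.714 | 29% |

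Keeping baseline as one of the repeated responses does not by itself give this gain. In an ordinary group-by-time linear model with complete data and no constraint at baseline, the month-3 difference between marginal means is the difference unadjusted for baseline C-ACT. The difference in change has relative variance 2(1 − r), which is 1.00 at r = 0.5 against 0.75 with adjustment. The gain comes when baseline is a covariate, or when it is a response whose mean is constrained equal across arms.

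**4. Illustration.** With 25 per arm, an assumed month-3 effect of 0.8 SD and r = 0.5, power is 0.81 at month 3 unadjusted and 0.90 adjusted. Without baseline adjustment, it is 0.37 (f = 0) to 0.53 (f = 0.25) pooled over the two later visits, and 0.21 to 0.30 pooled over all three. These values only rank the options; the trial states no effect size.

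**5. Parenting style.** Section 2.12 names it as a covariate and Table 1 supplies three values per child. No passage restricts the model to the time-0 value, and none says that later values are used.

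**The case against.** The strongest reply is that an unspecified contrast is not a faulty one. A group-by-time model with a month-3 contrast of marginal means fits sections 2.9.1 and 2.12 as printed and loses none of the effect, and the Discussion points to the post-intervention score. An article may also leave exact model terms to an analysis plan that is not shown. This stands against the stronger reading a reader might draw, that the planned analysis dilutes the 3-month effect: no passage says that visits are pooled. It does not remove the need to name the contrast. The article prints the model family, the covariates, the package and the method of comparison, yet leaves open the visit on which the primary result rests.

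A second reply is that baseline is already among the repeated measurements, and that omitting it as a covariate does not bias a randomised comparison. The point about bias stands. The point about precision stands only if baseline means are constrained equal across arms, which is not stated.

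Third, the variance formulas are for a continuous score, whereas the printed model is negative binomial for symptom frequency. That is correct, so the percentages indicate size on the score scale and do not describe the printed model. The gap between a C-ACT outcome and a count model is itself a reason to state the primary contrast on the score.

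Fourth, section 2.4 says that the pilot is not meant for hypothesis testing. That lowers the stakes for power. The same section, however, sets the size so that outcome variability can be determined, and section 2.12 sets a 0.05 level.

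**Conclusion.** The concern holds in conditional form. The primary outcome is spread over three C-ACT visits without a named contrast, and the printed covariates omit baseline C-ACT and leave the timing of parenting style open.

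If one effect were pooled over the two later visits, about half of the 3-month effect would remain when discharge shows none, and 63% when discharge shows a quarter of it. With a month-3 contrast from a group-by-time model there is no dilution. What is then lost, without baseline adjustment or equal baseline means, is precision: adjustment would cut the standard error by 5% to 29% for r between 0.3 and 0.7.

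These sizes rest on assumed values of f and r. That most of the recall at discharge precedes admission holds for stays under 14 days and for the parent items only. It should not be inferred that discharge C-ACT as a whole can show no effect, because the child items have no stated window. Nor should it be inferred that parenting style after allocation will be adjusted for; the text only fails to rule it out.

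**What to change.** In sections 2.9.1 and 2.12:

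- State the primary contrast as the between-arm difference in C-ACT score at 3 months, adjusted for baseline C-ACT. Baseline may enter as a covariate, or as a response with means constrained equal across arms; say which. Use a model that suits the score.
- Report discharge C-ACT as supportive data and use it as an auxiliary variable in the multiple imputation.
- If parenting style stays in the model, enter only its time-0 value.

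This takes one paragraph. Every variable is already scheduled in Table 1, so no new data are needed.
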